### Economic evaluation

The economic evaluation (cost effectiveness and cost utility analysis) will be performed according to the intention-to-treat principle and from a societal perspective. Healthcare costs (costs of hospitalisation, medication), costs in other sectors, patient and family costs, and costs of production losses are included. Quality adjusted life years (QALYs) are used as the main health outcome measure for the cost-utility analysis. Incremental cost effectiveness ratios (ICER) will be estimated using bootstrapping techniques and graphically presented on cost effectiveness planes. Sensitivity analysis on the most important assumptions will be performed in order to assess the robustness of the results.

QALYs will be calculated as the area under the health utility profile, with straight-line interpolation between utilities at each follow up. Utilities will be obtained using the EuroQol (EQ-5D) instrument. Health states will be estimated using reference values from a representative Dutch sample. ICER will be estimated using bootstrapping techniques and graphically presented on cost effectiveness planes. Sensitivity analysis on the most important assumptions will be performed in order to assess the robustness of the results.

The input of the implementation strategies will be assessed by collecting volumes of consumed resources and multiplying these by the price of each resource unit (market or guideline price). The output of the implementation strategies will be determined by the guidelines adoption rate, measured at fixed intervals during the study and the speed of adoption. Welfare losses will be determined by empirically established diffusion curves (one diffusion curve per strategy) and quantified by calculating the welfare change (monetarized variation in indicators/benchmarks compared to guideline) at the different time intervals adjusted for the complement of the adoption rate at a particular time interval. The decision criterion on which the efficient implementation strategy will be selected is the minimum welfare loss compared to the guideline programme over time (dynamic efficiency). The impact of variable(s) uncertainty on the decision criterion will be evaluated by sensitivity analyses.

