**Methods/Design:**

The objective of this study is to assess the cost effectiveness of an innovative implementation strategy of the NVOG guidelines on hypertension including a computerised decision support system (BOS) compared to a common strategy of professional audit and feedback. A cluster randomised controlled trial with an economic evaluation alongside will be performed. Both pregnant women who develop severe hypertension or pre-eclampsia and professionals involved in the care for these women will participate. The main outcome measures are a combined rate of major maternal complications and process indicators extracted from the guidelines. A total of 472 patients will be included in both groups. For analysis, descriptive as well as regression techniques will be used. A cost effectiveness and cost utility analysis will be performed according to the intention-to-treat principle and from a societal perspective. Cost effectiveness ratios will be calculated using bootstrapping techniques.

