It is thought that a high degree of these maternal complications results from suboptimal or insufficient treatment [12,13]. A recent study of the Dutch Committee on Maternal Death showed that in 96% of the cases of maternal death due to hypertensive disease several factors of substandard care were present. For instance, in 85% of this patient group, treatment of severe hypertension was inadequate. In many cases, the decision to start therapy was either made too late or not at all [14]. Therefore, management of hypertension is an important part of care for pregnant women for which improvement is necessary. To support their members, the Dutch Society of Obstetrics and Gynaecology (NVOG) has developed evidence-based clinical guidelines on the management of hypertension in pregnancy [15] and chronic hypertension in pregnancy [16]. However, these guidelines are not yet implemented. The NVOG has no general strategy of practical implementation and evaluation of its guidelines, and has only just begun with a policy of hospital visitations in order to improve quality of clinical care. In order to reduce maternal complications, an implementation strategy to improve adherence to the guidelines on hypertension in pregnancy is necessary

Original studies and systematic reviews about the effectiveness of different interventions to change clinical practice show that a widely used strategy for implementing guidelines consists of audit and feedback about actual performance. This strategy has shown to be effective, but feedback is often recommended in combination with other strategies [17]. In a recent systematic review, a major benefit of implementing health information technology on increased adherence to guideline-based care was demonstrated, including hypertension [18]. Different health information technology systems were reviewed. Most of them included a decision support system, and some of them integrated clinical guidelines [19]. In case of hypertension in pregnancy, an implementation strategy including a computerised decision support system (BOS) may lead to a higher compliance to the guidelines' recommendations and thus a lower rate of maternal complications and their costs. This will be tested in this study.

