It is expected that an increased adherence to the guidelines' recommendations will reduce the number of major maternal complications. By reducing the number of major maternal complications, we expect a reduction in health care costs (*e.g*., costs of hospitalisation, medication), costs in other sectors, patient and family costs, and costs of production losses [20]. Estimating the size of this cost reduction is an essential part of this study.

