### Sample size

The rate of major maternal complications in 216 Dutch patients with severe hypertension or preeclampsia was reported as 34% [7,8]. In 96% of cases of maternal death, care was suboptimal with insufficient treatment of hypertension in about half of these [14]. It is expected that an increased adherence to the guidelines' recommendations will reduce the number of major maternal complications by one-half, *i.e*., from 34% to 17%. Considering an intracluster correlation of 0.05, 20 hospitals will have to be included with approximately 20 patients each in order to get a reliable estimate (alpha = 0.05; power = 0.80) of a 50%-difference (34 verus 17%) in major maternal complications between both groups. If it is assumed that 15% of participants will drop out or be lost to follow up, 472 eligible women will have to be included. It also is assumed that the total number of deliveries in the participating hospitals is 30,000 (during 18 months of inclusion in 20 hospitals) and the incidence of severe hypertension and preeclampsia is 2%. It is estimated that the source

population consists of 600 eligible women. Thus, the expected number of inclusions per month will be 33 in 20 hospitals, *i.e*., one or two per hospital. The minimum required number of inclusions for randomisation per month is 26 [see figure 1 for flowchart].

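### The cost-effectiveness and cost-utility analyses are summarised numerically only by a bootstrapped ICER, which cannot be ordered in the quadrant where the plan expects the result to fall.

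*Protocol article*

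**What the plan says.** Research questions 1 and 3 (Objectives) both ask about cost effectiveness. The Abstract answers with "Cost effectiveness ratios will be calculated using bootstrapping techniques", and the Implementation study section repeats this. The Economic evaluation section is more specific: "Incremental cost effectiveness ratios (ICER) will be estimated using bootstrapping techniques and graphically presented on cost effectiveness planes". It says so twice, covers both a cost-effectiveness and a cost-utility analysis, and makes QALYs the main outcome of the latter. Patients are followed for six months after delivery (Implementation study).

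The Background gives the expected direction. BOS may lead to better guideline compliance and "thus a lower rate of maternal complications and their costs". It continues: "By reducing the number of major maternal complications, we expect a reduction in health care costs". The costs of the two strategies are also to be collected, but no total net cost difference is forecast.

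The same section sets a separate criterion for choosing the efficient strategy: minimum welfare loss over time, built from guideline adoption rates and diffusion curves.

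**The concern.** An ICER can be read as a price per unit of benefit only when the cost and effect differences have the same sign. If one strategy is both better and cheaper, the ratio is negative. A more negative value may then mean a larger saving (better) or a smaller benefit (worse). A strategy that is worse and dearer gives negative values too. The plan expects fewer complications and lower complication costs, so its hoped-for result may lie exactly where its numerical summary stops being informative.

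A second issue concerns the denominator. A bootstrapped ratio behaves badly when the effect difference is small relative to its error, because replicates then fall on both sides of zero. Few QALYs can accrue in six months, so this could affect the cost-utility analysis.

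At stake is how clearly the patient-level economic questions are answered. The validity of the bootstrap and the plane is not in doubt.

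**Working it through.** **The plan's own figure.** The economic section states no number, so the sample size is reproduced to fix the precision. The inputs are in Sample size: 34% v 17%, "alpha = 0.05; power = 0.80", and "Considering an intracluster correlation of 0.05, 20 hospitals will have to be included with approximately 20 patients each".
- Two proportions, two-sided, pooled, no continuity correction: just over 102 per arm, rounded up to 103.
- Design effect: 1 + (20 - 1) x 0.05 = 1.95.
- Total: 2 x 103 x 1.95 = 401.7.
- With 15% dropout: 402 / 0.85 = 473, or 401 / 0.85 = 472. The stated 472 is reproduced.

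The steps below use 200 analysed women per arm and the design effect of 1.95.

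**Ordering of the ratio.** The values are chosen for illustration. Effect is coded as benefit.

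| Cost difference | Effect difference | Ratio |
|---|---|---|
| -600 | +0.005 QALY | -120,000 |
| +600 | -0.005 QALY | -120,000 |
| -600 | +0.010 QALY | -60,000 |

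The first two rows are opposite results with the same ratio. The third is better than the first, yet its ratio is closer to zero.

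The same happens per complication averted. Net benefit here uses an assumed value of 10,000 per complication averted: 10,000 x effect difference - cost difference.

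| Cost difference | Complications averted per woman | Ratio | Net benefit |
|---|---|---|---|
| -1,000 | 0.17 | -5,882 | 2,700 |
| -1,000 | 0.085 | -11,765 | 1,850 |
| -2,000 | 0.17 | -11,765 | 3,700 |
| +1,000 | -0.17 | -5,882 | -2,700 |

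Net benefit separates all four rows; the ratio gives only two values. Coding the effect as a change in complication rate flips the sign but leaves the ambiguity.

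**Denominator, complications averted.**
- SE = sqrt((0.34 x 0.66 + 0.17 x 0.83) / 200 x 1.95) = 0.060.
- 0.17 / 0.060 = 2.85 SE from zero, so about 0.2% of draws have a negative denominator.

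**Denominator, QALYs.** The documents give no QALY figures. Assume an SD of 0.08 and 0.02 to 0.10 QALY lost per complication.
- SE = sqrt(2 x 0.08² / 200 x 1.95) = 0.0112.

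| QALY lost per complication (assumed) | Mean difference | SE from zero | Draws with negative denominator |
|---|---|---|---|
| 0.02 | 0.17 x 0.02 = 0.0034 | 0.30 | about 38% |
| 0.05 | 0.17 x 0.05 = 0.0085 | 0.76 | about 22% |
| 0.10 | 0.17 x 0.10 = 0.0170 | 1.52 | about 6% |

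These shares are for draws centred on the true difference. Bootstrapping around an estimated difference adds that estimate's own error. At 0.05 QALY this gives 0.76 / sqrt(2) = 0.54 SE, or about 30% on average.

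**The case against.** The strongest reply is that the article states nothing false. It plans the cost-effectiveness plane, which puts a dominant and a dominated result in opposite quadrants, so a reader of the plane is not misled. Nothing bars reporting dominance. Net benefit, an acceptability curve and a willingness-to-pay range are details that a condensed article may leave to a fuller plan. Most of this stands, and their absence is not the point here. The point is the summary that the article does fix, which it repeats in several places and which does not suit the result it expects.

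Some stronger readings are tempting but are not supported:

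- **An uninterpretable confidence interval is planned for the ICER.** A reader might infer this from the bootstrap. The article states no interval for the ratio, and the uncertainty display it names is the plane.
- **The denominator is unstable throughout.** It is not for complications averted under the planned effect. For QALYs it rests on assumed values.
- **The ICER is the only basis for a decision.** Minimum welfare loss is the stated criterion for choosing a strategy. It does not fill the gap, however, because it rests on guideline adoption over time and does not summarise patient-level costs and QALYs.
- **The result is certain to be negative.** The expected saving concerns costs that follow from complications. Strategy costs also count, and the net sign is not forecast.
- **Net benefit would settle whether BOS is worth its cost.** Assume EUR 6,000 per complication, EUR 400 strategy cost per woman, 0.05 QALY per complication and EUR 20,000 per QALY. Expected net benefit is then 20,000 x 0.0085 + (0.17 x 6,000 - 400) = 170 + 620 = EUR 790. A simulation that also assumed a cost SD of EUR 6,000 and a QALY SD of 0.08 gave an interval about EUR 3,500 wide, which around 790 includes zero. The gain is an estimate that can be interpreted, not a decisive one.

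**Conclusion.** The concern holds in a limited form. The ordering problem is pure arithmetic and needs no assumption beyond the plan's expectation of fewer complications together with a net saving. There the ratio and its bootstrap distribution are a poor numerical summary, although the plane shows the quadrants. The denominator problem is plausible for the cost-utility analysis only: roughly 6% to 38% of draws under the assumed QALY values, against about 0.2% for complications. All euro figures are illustrative, because the documents give no costs. This is a cheap improvement of modest importance. It is not an error that invalidates the economic evaluation.

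**What to change.** Keep the bootstrap and the plane, and change the numerical summary:

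- Report incremental cost and incremental effect separately, each with an interval.
- Summarise the cost-utility analysis by incremental net monetary benefit with its interval, or by an acceptability curve, over a pre-stated willingness-to-pay range. Do the same per complication averted for the cost-effectiveness analysis.
- Give the ICER only as the ratio of the mean differences, and only when both have the same sign. Otherwise report dominance.

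This takes one paragraph and uses the same bootstrap replicates. The downside is that the investigators must commit to a willingness-to-pay range, including one for a complication averted.

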## Methods/Design

### Study design

A cluster randomised controlled trial with an economic evaluation alongside will be performed. The chosen implementation strategies are:

1. A common strategy consisting of professional audit and feedback.

2. An innovative strategy including a BOS tailored to the barriers and facilitators that are found in a pilot study and professional audit and feedback.

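### The efficient strategy is the one with the smaller of two welfare losses, and no between-hospital sampling error is carried into that choice

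*Protocol article*

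**What the plan says.** The design is a cluster randomised trial: "A cluster randomised controlled trial with an economic evaluation alongside will be performed". The Sample size section takes hospitals as the clusters: 20 of them, about 20 patients each, with an intracluster correlation of 0.05.

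The last paragraph of Economic evaluation then sets out a separate criterion for choosing between the strategies:

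- The output of each strategy is the "guidelines adoption rate, measured at fixed intervals during the study and the speed of adoption".
- Welfare loss is derived from "empirically established diffusion curves (one diffusion curve per strategy", with the welfare change in each interval "adjusted for the complement of the adoption rate at a particular time interval".
- The efficient strategy is the one with "the minimum welfare loss compared to the guideline programme over time (dynamic efficiency".
- For uncertainty: "The impact of variable(s) uncertainty on the decision criterion will be evaluated by sensitivity analyses".

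Bootstrapping appears in the same section, but only for the incremental cost-effectiveness ratio ("ICER) will be estimated using bootstrapping techniques and graphically presented on cost effectiveness planes"), and no resampling unit is named.

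**The concern.** One curve per strategy gives one welfare loss per strategy. Barring an exact tie, one of the two is smaller, so the rule names a winner even when the strategies are equally good. Whether the gap exceeds what hospital-to-hospital variation would produce is a question of sampling error, and the hospital is the unit that carries it.

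A sensitivity analysis that varies prices, weights or other inputs shows how the answer depends on those inputs. It does not show how the answer would change with a different set of hospitals. The plan allows for hospital variation when it sizes the trial and states no such allowance when it selects the strategy. Cost effectiveness is the declared objective, so a difference that is ordinary hospital variation could be reported as the finding that one strategy is efficient.

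**Working it through.** **1. The plan's own figure.** Inputs from Sample size: 34% versus 17%, alpha 0.05 (taken as two-sided), power 0.80, intracluster correlation 0.05, about 20 patients per hospital, 15% dropout.

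- Per arm before clustering, with mean proportion 0.255: [1.96 × √(2 × 0.255 × 0.745) + 0.8416 × √(0.34 × 0.66 + 0.17 × 0.83)]² / 0.17² = 1.71694² / 0.0289, just above 102, rounded up to 103.
- Design effect: 1 + (20 − 1) × 0.05 = 1.95.
- 103 × 1.95 = 200.85, or about 10 hospitals of 20 patients per arm.
- Dropout: 200 / 0.85 = 235.3, rounded up to 236; 2 × 236 = 472.

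The stated 472 reproduces. It fits 10 hospitals per arm, a number that the article does not state.

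**2. Which uncertainty method goes with which quantity.**

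- Cost-effectiveness ratio: bootstrap, unit not stated.
- Primary and secondary outcomes and process indicators: a multi-level analysis (Data analysis section) whose named levels are gynaecologist, patient and time. Hospital is not named, and the analysis is not linked to welfare loss.
- Welfare-loss criterion: sensitivity analyses, type not stated.

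**3. Scale of the missing error, on adoption.** SE of the arm difference = √[2 × p(1 − p) × (1 + 19 × ICC) / 200]. The article gives no adoption rate and no correlation for adherence, so p = 0.60 is assumed and 0.05 is borrowed from the complications calculation.

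- Hospitals ignored: √(2 × 0.24 / 200) = 0.049.
- ICC 0.05: √(2 × 0.24 × 1.95 / 200) = 0.068.
- ICC 0.10: √(2 × 0.24 × 2.90 / 200) = 0.083.
- At ICC 0.05 with p = 0.50 or 0.70: 0.070 or 0.064.

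The ratio to the naive error at ICC 0.05 is √1.95 = 1.40, whatever the adoption rate. Suppose one strategy truly has 5 points more adoption. Picking the arm that looks better is then wrong with probability Φ(−5/6.84) = 0.23, where the naive error would suggest Φ(−5/4.90) = 0.15. These are errors of an adoption difference, not of the welfare loss itself.

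**4. The same on the loss scale, by illustration.** Assume logistic adoption with equal speed in all hospitals, 10 hospitals per arm, midpoints that vary between hospitals with SD s months, and loss equal to the time integral of non-adoption. Over a long enough horizon the loss is about the midpoint, so the SE of the arm difference is s × √(2/10): 0.45, 0.89, 1.34 and 1.79 months for s = 1, 2, 3 and 4. With a true one-month advantage, the rule picks the wrong strategy with probability Φ(−1/SE), about 1%, 13%, 23% and 29%. The article gives no value of s.

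**5. Does averaging hospitals into one curve bias the criterion?** With a welfare weight w(t) common to the hospitals, loss = Σ w(t) × [1 − mean adoption(t)] = mean over hospitals of Σ w(t) × [1 − adoption(t)]. The two sides are identical because loss is linear in non-adoption. In a simulation under assumptions like those in step 4 (speed 0.6 per month, mean midpoint 9 months, 18-month horizon), replacing the mean curve by a single fitted logistic changed the loss by less than 0.001 month. The slope of the average curve does fall below the within-hospital slope when timing varies. Under the same assumptions it was 0.95, 0.82, 0.70 and 0.59 of that slope for s = 1 to 4. It was unchanged when there was no timing spread or when hospitals differed only in plateau.

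**The case against.** The strongest reply has three parts.

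- **Condensed text.** The article does plan to examine uncertainty in the criterion, and an unspecified sensitivity analysis could be probabilistic. The single curve could also be the mean curve of a model with hospital effects. Both readings are possible, but the text states neither, and it gives a bootstrap to the cost-effectiveness ratio without extending it to the loss.
- **A decision rule needs no test.** Someone who must choose one strategy may reasonably take the lower expected loss whatever its interval. That stands as a defence of the rule. It does not remove the need to say how secure the choice is.
- **Limited reach.** This is an economic criterion, not the primary outcome. That stands and limits the severity.

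A reader might go further and infer that a single curve per strategy flattens adoption, understates its speed and so distorts the choice, particularly if the computerised system is rolled out unevenly. The article does not support this. It gives no spread in adoption timing and describes no staggered start, and its wording does not fix a naive pooled fit. Step 5 shows that averaging leaves the loss essentially unchanged. The average curve is also the proper description of a strategy as a whole. Only speed read as the speed within a hospital could be understated, and only if hospitals differ in timing.

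**Conclusion.** The point holds in a limited form. As written, the efficient strategy is chosen by comparing two point values, and nothing stated carries between-hospital sampling error into that comparison, although the trial's own sample size assumes clustering. At the borrowed correlation of 0.05 and about 20 women per hospital, the standard error of an adoption difference is 1.4 times the naive one: about 6.8 against 4.9 points at 60% adoption, and 8.3 if the correlation is 0.10. These sizes rest on an assumed adoption rate, on a correlation set for complications rather than adherence, and on an inferred 10 hospitals per arm. They indicate scale and do not measure the error of the loss. The primary outcome is not affected.

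**What to change.** Keep the average curve per strategy, count time from allocation, and keep the planned sensitivity analyses. Add a bootstrap that resamples whole hospitals within each arm and repeats every step in each replicate: adoption by interval, curve, welfare change and loss. Report a hospital-level interval for the loss difference and the probability that each strategy has the lower loss.

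Two alternatives are less suitable. Resetting time to each hospital's own start would drop any delay before start, which is a real loss over time. Random slopes by hospital would be fragile: with six three-month intervals (assumed) in the 18 months of inclusion, there are 472 / 20 / 6 = 3.9 women per hospital per interval.

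Also state what speed of adoption means. If it is speed within a hospital, note that an average curve understates it when hospitals differ in timing.

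The change needs analysis wording and some computing on data already planned. Its price is a wider, possibly inconclusive, interval around the chosen strategy, and a bootstrap that is itself imprecise with about 10 hospitals per arm.

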### Interventions

Innovative strategy including a computerised decision support system. We performed a pilot-study to make an inventory of the barriers and facilitators for adherence to the guidelines on hypertension in pregnancy. Barriers can arise at different stages in the healthcare system at the level of the individual professional (*i.e*., lack of knowledge or skills, resistance against working with protocols); of the healthcare team (*i.e*., lack of knowledge or skills, insufficient collaboration); of the patient (*i.e*., unwillingness, difficult guideline adherence for some patient groupes); of the healthcare organisation (*i.e*., lack of registration/information systems, time restriction for adequate care); and of the wider environment (*i.e*., lack of financial incentives, misuse of guideline in medical disciplinary law) [20]. Barriers can also arise at the level of the innovation (guideline) itself (*i.e*., doubting evidence of the guideline, poor layout, unclear decision tree, unclear content). In a pre-study among 14 gynaecologists in 11 different hospitals (university medical centres, teaching and non-teaching hospitals), we determined which barriers at which level were present regarding the implementation of the guidelines on hypertension in pregnancy. The main barriers proved to be at the level of the guideline itself. A poor layout to use the guideline showed the highest score (64%). Doubt about a clear decision tree behind the guideline scored also high (57%). Furthermore, 36% of the gynaecologists mentioned that 'the guideline could easy be misused in medical disciplinary law,' 'the content of the guideline was unclear,' and that 'there was not enough room to consider patients wishes.' Moreover, 50% of the gynaecologists doubted about the accuracy of certain parts of the guideline. The implementation strategy will be based on these barriers and facilitators. We will use a computerised decision support system, which is a commercial web application developed by Giant-Soft in Leeuwarden, the Netherlands. A similar system has been tested and evaluated using another clinical guideline. The system appeared feasible in clinical practice: most users (95%; 34 of 36) were satisfied with its use and 78% (28 of 36) would prefer to maintain and extend the application to other guidelines [23,24]. In our opinion, BOS can be a solution for the main barriers regarding layout of, and decision tree behind, the guideline. In this way, BOS is tailored to the barriers 'possible misuse in the medical disciplinary law' and 'not enough room to consider patients' wishes.' In this strategy, we will combine BOS with professional audit and feedback (see control intervention).

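### As worded, the criterion for choosing the efficient implementation strategy has no term for the cost of delivering the strategies

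*Protocol article*

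**What the plan says.** The relevant text is the last paragraph of the Economic evaluation section of the protocol article. It proceeds in four steps.

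- Strategy cost: "The input of the implementation strategies will be assessed by collecting volumes of consumed resources and multiplying these by the price of each resource unit".
- Strategy result: the rate and speed of guideline adoption, measured at fixed intervals.
- Welfare loss: "Welfare losses will be determined by empirically established diffusion curves (one diffusion curve per strategy"). Its size is obtained as follows: "calculating the welfare change (monetarized variation in indicators/benchmarks compared to guideline) at the different time intervals adjusted for the complement of the adoption rate".
- Choice: "The decision criterion on which the efficient implementation strategy will be selected is the minimum welfare loss compared to the guideline programme over time". The uncertainty of unnamed variables in this criterion is to be examined by sensitivity analyses.

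The Interventions section describes the system: "We will use a computerised decision support system, which is a commercial web application". It adds: "In this strategy, we will combine BOS with professional audit and feedback (see control intervention"). The Control intervention section gives the other arm audit and feedback only.

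Earlier in the Economic evaluation section, a cost effectiveness and cost utility analysis is planned from a societal perspective, with bootstrapped ICERs shown on cost effectiveness planes. The cost categories listed there are health care, other sectors, patient and family, and production losses.

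**The concern.** Research questions 1 and 3 in the Objectives ask about cost effectiveness. The only explicit rule for choosing a strategy is the welfare-loss criterion. Strategy cost is priced at the start of that paragraph, but no later sentence takes it into the welfare loss or the choice.

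The two strategies are nested: one is the other plus a commercial product. If audit and feedback costs the same in both arms, the innovative strategy costs at least as much to deliver. With equal welfare losses and any positive extra cost, the cheaper strategy is the efficient one. A criterion with no cost term cannot reach that conclusion. The trial could thus name BOS the efficient strategy on a chance difference in losses, or on a real gain smaller than its price.

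**Working it through.** **1. The rule in symbols.** The article gives no formula, so this is a reading of its words. Let *L* be a strategy's welfare loss and *C* its priced input. From the Interventions and Control intervention sections, C(BOS arm) = C(control) + *c*, with *c* ≥ 0 if audit and feedback costs the same in both arms. Let *D* = L(control) − L(BOS arm).

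- Criterion as worded: choose BOS if *D* > 0.
- Criterion with delivery cost: choose BOS if *D* > *c*.

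The two disagree whenever 0 < *D* < *c*, and the worded criterion then picks BOS at a net loss. The break-even cost is *c* = *D*. This step needs no assumed adoption level, ICC or price.

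**2. No true difference.** If the arms are equal in size and truly alike, the two estimated losses are exchangeable, so the probability that *D* > 0 is one half. Since *c* does not enter, this holds at any price. It assumes that the criterion is applied as a bare comparison; the article attaches no threshold to it.

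**3. The plan's own figures.** The criterion has no stated error rate to reproduce. The Sample size section can be checked, because its design is used below. For 34% versus 17%, two-sided alpha 0.05 and power 0.80, the normal approximation gives 103 women per arm. The design effect is 1 + (20 − 1) × 0.05 = 1.95. Then 2 × 103 × 1.95 = 401.7, and 401.7 / 0.85 = 472.6, against 472 stated. The design figures reproduce within rounding.

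**4. Illustration only.** Assumed: 10 hospitals per arm (the article gives 20 in total, and equal allocation is assumed); 20 women each; ICC 0.05 (stated for complications, borrowed here for adherence); adoption 50% under control; and the same value *V* per adherent woman in both arms, with no timing effect. Under these assumptions the loss difference is *V* times the adoption difference.

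SD of the adoption difference = √(2 × 0.5 × 0.5 × 1.95 / 200) = √0.004875 ≈ 0.070.

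For a 5-point gain, 0.05 / 0.070 ≈ 0.72, a probability of about 0.76. Simulating 40,000 trials per scenario gives:

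| True adoption gain | Extra BOS cost per woman | BOS chosen, as worded | BOS chosen, cost added |
|---|---|---|---|
| 0 | 0.1 V | 50% | 8% |
| 5 points | 0.1 V (net loss 0.05 V) | 76% | 23% |
| 10 points | 0.2 V (net loss 0.1 V) | 92% | 7% |

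A second simulation uses four intervals with assumed adoption rising from 40% to 70% and no true difference. The worded criterion chooses BOS 50% of the time at extra costs of 0, 0.05 V, 0.1 V and 0.3 V. With the cost added, the figures are 50%, 23%, 7% and 0%.

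**The case against.** The strongest reply is that the article condenses a fuller protocol. A paragraph that prices inputs, names outputs and ends in an efficiency criterion may have been meant to net cost against loss. That is plausible, and the text does not say that cost is deliberately excluded. But the article does not defer the rule elsewhere. It says how the loss is built and what decides the choice, and neither statement includes the input.

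A second reply is that the ICER and cost-utility analysis addresses cost. This stands in part: a reader might infer that the whole economic evaluation ignores cost, and that is not so. The ICER may well show BOS to be expensive. It carries no threshold or selection rule, however, and its listed cost categories do not name implementation cost, so it does not replace the stated criterion.

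Three stronger readings are not supported.

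- A reader might infer that the criterion simply picks the arm with higher observed adoption. Welfare loss also depends on the monetarised indicator variation and on when adoption occurs, so this holds only if value per adherent woman and timing are the same in both arms.
- A reader might infer that a corrected rule would almost never choose an ineffective BOS. The illustrations give 7% to 8% at 0.1 V, 23% at 0.05 V and 50% at zero extra cost.
- A reader might infer that the sensitivity analyses cannot vary strategy cost. The article does not list the variables. Even so, varying a cost that is absent from the criterion would leave the choice unchanged.

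**Conclusion.** The point holds for the selection criterion as worded: delivery cost is priced but cannot affect which strategy is called efficient. That conclusion rests on the text alone, together with the nesting of the two strategies.

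The figure of about one half under no true difference rests on equal arms and a bare comparison of losses. The 76% and 92%, and all results with a cost added, are illustrations and not properties of this trial. The article gives no BOS price, no adoption level and no ICC for adherence, so the actual size of the error is unknown.

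The defect lies in one part of the economic evaluation. It does not touch the comparison of major maternal complications. It should be corrected because the criterion is the plan's only stated rule for choosing between the strategies.

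**What to change.** Restate the criterion in the Economic evaluation section along these lines: *The efficient strategy is the one with the lowest sum of welfare loss and priced strategy input, both taken over the same period and the same population of eligible women.*

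With it:

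- Report the between-strategy difference in this sum with uncertainty that respects hospital clustering, for example by resampling whole hospitals.
- Vary the BOS unit cost in the sensitivity analysis and report the break-even value at which the choice changes.
- Say how the criterion relates to the ICER analysis, and whether strategy costs are counted there.

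The cost is a sentence or two of text and one added term in the calculation. Strategy resource use is already to be collected and priced. The downside is that BOS may look somewhat less favourable than under the present wording.
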